#### Decisional regret

Decisional regret will be measured using the Decisional Regret Scale, measured at 12 months after the start of the second stage only [36].

### Statistical analysis

All statistical analyses will be performed using statistical software, such as SPSS and R. Univariable and multivariable regression analysis to correct for possible confounders will be used to compare groups. Longitudinal data will be analysed with linear and logistic mixed models and presented as estimated coefficients and odds ratios with 95% confidence intervals. Cumulative incidence of hospitalisation and mortality will be reported in Kaplan Meier curves. A Cox proportional hazards model will be used to compare the rate of mortality and hospitalisation between groups. Overall costs and ICERs will be compared across the two groups using linear regression. Discounting, a mathematical procedure for adjusting future costs to their ‘present day value’, will be applied, as requested for all health economic evaluation exceeding a time frame of 1 year. To deal with missing data, multiple imputation by fully conditional specification will be applied.

### Sample size calculation

For the primary outcome, we aim to have 80% power to detect a difference of 3.0 points in the SF-12 summary scores 12 months after the start of the second stage. To reject the null hypothesis of equal means with a standard deviation for both groups of 9.0 with a significance level (alpha) of 0.05 using a two-sided two-sample equal-variance Z-test, a required total sample size of 443 patients was calculated (89 patients on CC, 354 on dialysis, 1:4 ratio based on unpublished data from three Dutch centres). When taking into account a dropout rate of 10%, 99 patients on CC and 394 on dialysis are needed, a total of 493 patients. Based on a study from the United States, we expected one third of patients to progress from stage one to two within 3 years, so a cohort of 1500 patients will be needed [49].

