**Methods:**

The *DIALysis or not: Outcomes in older kidney patients with GerIatriC Assessment* (DIALOGICA) study is a prospective, observational cohort study that started in February 2020. It aims to include 1500 patients from 25 Dutch and Belgian centres. Patients aged ≥70 years with an eGFR of 10–15 mL/min/1.73m^2^ are enrolled in the first stage of the study. When dialysis is initiated or eGFR drops to 10 mL/min/1.73m^2^ or lower, the second stage of the study commences. In both stages nephrogeriatric assessments will be performed annually, consisting of questionnaires and tests to assess most common geriatric domains, i.e. functional, psychological, somatic, and social status. The primary outcome is HRQoL, measured with the Twelve-item Short-Form Health Survey. Secondary outcomes are clinical outcomes (mortality, hospitalisation, functional status, cognitive functioning, frailty), cost-effectiveness, and decisional regret. All outcomes are (repeated) measures during the first year of the second stage. The total follow-up will be a maximum of 4 years with a minimum of 1 year in the second stage.

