**Fig. 1 Fig1:**
[figure not shown]
Study flow chart. Abbreviations: *eGFR* estimated Glomerular Filtration Rate, *HRQoL* Health-Related Quality of Life, *NGA* NephroGeriatric Assessment

DIALOGICA is aimed to run for a total of 4 years with a minimum follow-up of 1 year in the second stage. The study is conducted according to the principles of the Declaration of Helsinki and the ICH-GCP guidelines. Primary ethical approval was obtained from the medical research ethics committee of the The Hague region (METC Zuidwest Holland) on May 24th 2019 (reference number 19–071). Local medical research ethics committees in participating centres will also be asked for local ethical approval. The study is registered in the Netherlands Trial Register under NL-8352.

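### The cohort of 1500 gives every patient a full 3 years to progress, but a 4-year study that reserves a year in stage 2 leaves 3 years for accrual and progression together.

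*Protocol article*

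**What the plan says.** All references are to the Protocol article.

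- **Sample size calculation, target.** The aim is "80% power to detect a difference of 3.0 points in the SF-12 summary scores 12 months after the start of the second stage", "with a standard deviation for both groups of 9.0 with a significance level (alpha) of 0.05", using a "two-sided two-sample equal-variance Z-test". The result is "a required total sample size of 443 patients was calculated (89 patients on CC, 354 on dialysis, 1:4 ratio".
- **Sample size calculation, dropout.** "When taking into account a dropout rate of 10%, 99 patients on CC and 394 on dialysis are needed, a total of 493 patients".
- **Sample size calculation, cohort.** "we expected one third of patients to progress from stage one to two within 3 years, so a cohort of 1500 patients will be needed".
- **Study design (text below Fig. 1).** "DIALOGICA is aimed to run for a total of 4 years with a minimum follow-up of 1 year in the second stage".
- **Abstract, Methods.** "The total follow-up will be a maximum of 4 years with a minimum of 1 year in the second stage".

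The first patient was recruited in February 2020, and 1500 patients are sought from at least 25 centres (Study design). The article gives no accrual length.

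**The concern.** The one-third figure is a 3-year proportion, and it is applied to all 1500 patients as if each had 3 years at risk of progressing. The primary comparison is made 12 months into stage 2, so in a 4-year study the last useful date for entering stage 2 is the end of year 3. A patient enrolled t years after the start has 3 − t years to progress, not 3.

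The calculation makes no allowance for this, and the spare margin is 7 patients in 500 (1.4%). If accrual takes any appreciable time, enrolling all 1500 with exactly 10% dropout would still leave the primary analysis short of the 443 evaluable patients on which the 80% power claim rests.

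**Working it through.** **1. Reproduce the plan's figures.** Inputs from Sample size calculation: difference 3.0, SD 9.0, two-sided alpha 0.05, power 80%, ratio 1:4.

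- CC group: n = (1 + 1/4) × [9 × (1.960 + 0.842)/3]² = 88.3, rounded up to 89.
- Total before rounding: 5 × 88.3 = 441.5. The plan's 443 (89 + 354) agrees within rounding and has 80.3% power.
- Dropout: 89/0.9 → 99; 354/0.9 → 394; total 493.
- Cohort: 493 × 3 = 1479, rounded to 1500; 1500/3 = 500.

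The chain 443 → 493 → 1500 is therefore sound, provided everyone has 3 years to progress.

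**2. Put in the calendar.** 4 years in total, less the final year needed for the 12-month outcome, leaves 3 years for accrual plus progression. With uniform accrual over A years, the expected fraction entering stage 2 in time is the average of F(3 − u) for u from 0 to A, where F(3) = 1/3.

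- Constant hazard: λ = −ln(2/3)/3 = 0.135 per year; fraction = 1 − [exp(−λ(3 − A)) − exp(−3λ)]/(λA).
- Linear progression: fraction = (3 − A/2)/9.

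Evaluable patients = 0.9 × entrants, split 1:4. Power = Φ(3/SE − 1.96), with SE = 9 × √(1/n_CC + 1/n_dialysis).

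Example, A = 1 year, constant hazard: fraction 0.286; entrants 429; evaluable 386 (77.3 and 309.0); SE = 1.145; 3/SE = 2.62; power = Φ(0.66) = 75%.

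**3. Results.** A is an assumed range, because the article does not state it. Entrants are those who can still complete 12 months.

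| Accrual A | Entrants, constant hazard (linear) | Evaluable | Power | Cohort needed for 493 entrants |
|---|---|---|---|---|
| 0 | 500 (500) | 450 (450) | 81% (81%) | 1480 (1479) |
| 6 months | 465 (458) | 419 (413) | 78% (77%) | 1589 (1614) |
| 1 year | 429 (417) | 386 (375) | 75% (73%) | 1723 (1775) |
| 2 years | 352 (333) | 317 (300) | 66% (64%) | 2103 (2219) |
| 3 years | 267 (250) | 240 (225) | 54% (52%) | 2772 (2958) |

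The comparison is with 493 entrants and 443 evaluable patients. Entrants fall below 493 once accrual exceeds about 1.2 months (constant hazard) or 1.0 month (linear).

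**4. Sensitivity to the shape of progression.** If progression is front-loaded but still one third at 3 years (Weibull shape 0.5, an assumption), entrants are 463, 418 and 350 for 1, 2 and 3 years of accrual, with power 78%, 73% and 66%. The shortfall is smaller but remains.

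**5. Could faster progression close the gap?** With a constant hazard, 493 entrants would need a 3-year progression of about 38%, 46% or 58% for 1, 2 or 3 years of accrual, against the planned one third.

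**6. Is near-immediate accrual plausible?** The Background gives over 1650 incident Dutch dialysis patients a year, 45% of them aged 70 or older: 0.45 × 1650 ≈ 740 a year. A cohort of 1500 is about twice that. Belgian patients and those who never start dialysis enlarge the pool, so this is only a rough guide, but enrolment of 1500 within a month or so is hard to credit.

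**The case against.** **The 4 years may be per patient.** The Abstract and Discussion use 4 years to describe follow-up, and 3 years to progress plus 1 year in stage 2 makes exactly 4. On that reading the cohort figure works. But both places give 4 years as an upper limit, which is also what staggered entry into a fixed-length study produces, and Study design says that the study itself runs 4 years. If the per-patient reading is intended, that sentence is wrong and the true duration is 4 years plus accrual. The alternative moves the correction elsewhere and does not remove it.

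**The size of the shortfall rests on assumptions.** This stands. Accrual length and the progression curve are not in the article, and the cited progression study could not be consulted. A reader might infer that the study must fall far short; the documents do not support that without an accrual length. At 6 months the loss is about 2 percentage points of power.

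**The planned analysis is not the Z-test.** This also stands. Statistical analysis plans mixed models, confounder adjustment and multiple imputation. Repeated measures could recover precision and confounder adjustment could cost some. The figures above test the stated power claim, which is made for the unadjusted Z-test; they do not forecast the power of the final model.

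**Mortality.** A reader might deduct the 18% first-year mortality in the Background as well. The documents do not support this step: the figure refers to patients who have started dialysis, not to CC, and the article does not say whether deaths are already within the 10% dropout.

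**The 4 years is an aim.** The wording leaves room to extend, but no extension is described and the sample size text does not rely on one.

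**Conclusion.** The concern holds in this form: the stated cohort size and power conflict with the stated study duration. The direction follows from the article's own figures. In a 4-year study with a reserved final year, 1500 patients do not yield 493 timely stage-2 entrants, or 443 evaluable patients, unless accrual takes about a month or less (about two and a half months on the front-loaded curve tried).

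The magnitude is conditional. With uniform accrual, a constant hazard, 10% dropout and a 1:4 ratio, power is about 78% at 6 months of accrual, 75% at 1 year, 66% at 2 years and 54% at 3 years, instead of 80%.

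**What to change.** **If the study runs 4 calendar years:** recalculate the expected stage-2 entrants from the planned accrual curve and the year-3 cut-off. State the accrual period, the expected entrants, and the resulting power or detectable difference. On the constant-hazard assumptions, the difference detectable with 80% power, (1.960 + 0.842) × SE, would be about 3.1 points at 6 months of accrual, 3.2 at 1 year, 3.5 at 2 years and 4.1 at 3 years. Monitor stage-2 entries against the restated figure.

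**If 4 years is meant per patient:** correct the sentence in Study design to give the true study duration, including accrual.

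**Alternative:** define study closure by the number of stage-2 entrants who have had 12 months of follow-up, not by a fixed date.

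**Cost:** the first option costs a few sentences and a less favourable stated power. Either of the others costs a longer study, which should be named as such.

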## Discussion

With an ageing population with kidney failure, more patients will face the decisional moment whether to start dialysis or not. As the survival benefit of dialysis treatment in the geriatric population is debatable, focus has shifted towards HRQoL as primary outcome measure. The impact of dialysis on HRQoL of older patients is probably large, but current data comparing it to CC are both limited and biased, creating an urgent need for high-quality studies [7]. DIALOGICA will be the first large study to prospectively assess the differences between patients choosing CC or dialysis. With a total follow-up of up to 4 years, outcome parameters can be assessed in more detail. Biological age, which also takes factors such as functional status, cognitive functioning, and somatic functioning into account, might influence these outcomes more than calendar age. This study will help to determine individual patient characteristics to identify patients less likely to benefit from dialysis initiation. This will support patients with kidney failure and their nephrologists in making a well-informed and shared decision when discussing renal replacement therapy. To do so, DIALOGICA combines a practical test set of well-validated questionnaires and assessments that can be performed in less than 1 hour per patient. With better identification of patients who might not benefit from dialysis, a significant reduction in costs for treatment of kidney failure can be achieved if these patients choose for CC, since CC has far lower annual treatment costs compared to dialysis [6].

DIALOGICA has an observational study design instead of a randomised controlled design. We deemed the patient’s choice between CC and dialysis too fundamentally different to let it be determined by fate. Randomised studies for treatment modalities have been shown to be challenging in patients with kidney failure in general as they have large and different implications for patients’ daily life. For example, a previous Dutch study that tried to randomise patients between haemodialysis and peritoneal dialysis failed and the choice whether or not to start dialysis arguably has even more impact [50]. To our knowledge, only one study comparing CC and dialysis is currently recruiting patients using a randomised design [51]. The implication of the observational design of DIALOGICA is that it is more sensitive to confounding by indication, since observed and unobserved variables can influence outcome of treatment. However, selective inclusion into randomised controlled studies can also lead to poor external validity of their results and an observational study may provide a better reflection of daily clinical practice. To account for the influence of the observed variables on treatment outcome and thus to limit confounding by indication, extensive correction for confounding will be applied, using a large set of patients’ characteristics.

Treating physicians and patients are not blinded for the results of the NGA, because this could hamper appropriate care for newly diagnosed geriatric impairments. Moreover, as NGAs are becoming standard of care in most Dutch centres, it is ethically undesirable to withhold the results of the NGA from treating physicians and participating patients. Since the results of the NGA might influence the treatment decision both for patients and for treating physicians this can introduce selection bias between patients choosing for CC and dialysis, and could be considered a limitation. Where needed, correction for baseline NGA discrepancies will be applied.

## Conclusion

Data on relevant outcomes are needed to answer the question whether CC is a serious alternative to dialysis in (a subgroup of) older patients with kidney failure. In the upcoming years, DIALOGICA will investigate the effect of CC on HRQoL, clinical outcomes, and cost-effectiveness in comparison to dialysis in this population, generating more insight to aid doctors and patients in the shared decision making process.

## Data Availability

Not applicable.

## Abbreviations

CC: Conservative Care
CKD-EPI: Chronic Kidney Disease EPIdemiology Collaboration
DIALOGICA: DIALysis or not - Outcomes in older kidney patients with GerIatriC Assessment
DSI: Dialysis Symptom Index
eGFR: Estimated Glomerular Filtration Rate
EQ-5D-5L: Five-level EQ-5D questionnaire
HRQoL: Health-Related Quality of Life
ICER: Incremental Cost-Effectiveness Ratio
iMCQ: iMTA Medical Consumption Questionnaire
iMTA: Institute for Medical Technology Assessment
iPCQ: iMTA Productivity Cost Questionnaire
NGA: NephroGeriatric Assessment
SF-12/− 36: 12/36-Item Short Form Health Survey
QALY: Quality adjusted life year
